## Abstract

**Background:**

Community-acquired pneumonia (CAP) remains a leading cause of hospitalization, morbidity, and mortality worldwide, particularly among older adults with multimorbidity and frailty. Despite advances in antimicrobial therapy, clinical outcomes have improved little, highlighting the need for safe, inexpensive adjunctive treatments. Vitamin C plays a critical role in immune function, redox homeostasis, and endothelial integrity, all disrupted during acute infection. Hypovitaminosis C is common in hospitalized patients with CAP and has been associated with increased disease severity, longer length of stay (LOS), and worse outcomes. However, prior randomized trials of vitamin C have produced inconsistent results, often focusing on critically ill patients with sepsis, using short treatment durations, and discontinuing therapy abruptly.

**Objective:**

The Vitamin C in Community-Acquired Pneumonia (VitCAP) trial aims to evaluate whether high-dose oral vitamin C administered over an extended period improves clinical recovery and patient-centered outcomes in adults hospitalized with CAP.

**Methods:**

VitCAP is a single-center, double-blind, placebo-controlled, parallel-group randomized clinical trial conducted at a tertiary hospital in Australia. Adults aged 18 years and older hospitalized with CAP will be randomized within 48 hours of admission in a 1:1 ratio to receive either oral sodium ascorbate (1 g 3 times daily for 7 days, followed by 500 mg twice daily for 30 days) or a matching placebo in addition to standard care. Randomization will be computer generated with allocation concealment via a centralized pharmacy service, and all participants, clinicians, investigators, and outcome assessors will remain blinded. The primary outcome is time to clinical stabilization, defined using standard physiological criteria. Secondary outcomes include early clinical response, symptom burden at 30 days, intensive care unit admission, need for ventilatory or vasopressor support, LOS, all-cause mortality at 30 days and 6 months, hospital readmission, health-related quality of life, and changes in inflammatory biomarkers (C-reactive protein and procalcitonin). Analyses will follow the intention-to-treat principle. The primary outcome will be analyzed using Cox proportional hazard regression adjusted for prespecified covariates, with sensitivity analyses including restricted mean survival time.

**Results:**

The VitCAP trial received ethics approval from the Southern Adelaide Local Health Network Human Research Ethics Committee in 2025 and funding in September 2025. Recruitment is expected to commence in 2026 and continue for 18 to 24 months. A total of 124 participants will be enrolled to provide 80% power to detect a clinically meaningful difference in time to clinical stabilization while allowing for attrition. Data analysis will follow completion of follow-up, with primary results anticipated in 2028.

**Conclusions:**

The VitCAP trial is designed to address important evidence gaps by evaluating sustained oral vitamin C supplementation in hospitalized patients with CAP using clinically meaningful patient-centered outcomes. If effective, vitamin C could represent a safe, low-cost, and scalable adjunct to standard CAP management.

**Trial Registration:**

Australian New Zealand Clinical Trials Registry (ANZCTR) ACTRN12625001361493; https://anzctr.org.au/Trial/Registration/TrialReview.aspx?ACTRN=12625001361493

**International Registered Report Identifier (IRRID):**

PRR1-10.2196/91037

## Introduction

### Background

Community-acquired pneumonia (CAP) is an acute infection of the pulmonary parenchyma that occurs outside the hospital setting and remains a major cause of hospitalization, morbidity, and mortality worldwide. Lower respiratory tract infections accounted for approximately 2.6 million deaths worldwide in 2019, ranking among the leading causes of death [1]. Population-based CAP studies from high-income countries report hospitalization rates of approximately 25 per 10,000 adults annually, with 20% to 25% of patients requiring intensive care unit (ICU) admission [2]. Mortality remains substantial, particularly among older adults and those with multimorbidity and frailty [3].

Recent Australian data highlight the persistent burden of CAP. In a large multicenter cohort of patients hospitalized with non–COVID-19 CAP, in-hospital and 30-day mortality rates were 7.8% and 16.9%, respectively, rising to 17.6% among those requiring ICU admission [4]. Despite advances in antimicrobial therapy and supportive care, outcomes have remained largely unchanged, underscoring the need for safe and effective adjunctive therapies to improve recovery and reduce complications.

### Rationale for Vitamin C Supplementation

Inflammation and oxidative stress are central to the pathophysiology of CAP and its complications, including respiratory failure and sepsis-related organ dysfunction, through the excessive production of reactive oxygen species and proinflammatory cytokines, with consequent tissue injury [5-7]. Vitamin C (ascorbate) is a key antioxidant with immunomodulatory properties; however, humans cannot synthesize it endogenously and rely entirely on dietary intake [8].

Hypovitaminosis C is common in acute illness due to increased metabolic demand, reduced intake, and enhanced losses and has been associated with worse outcomes in sepsis and pneumonia [9-11]. Among hospitalized patients with CAP, our research [12] suggests that 42.6% are vitamin C deficient and these patients had 23% longer hospital length of stay (LOS; incidence rate ratio=1.23, 95% CI 1.06-1.42; *P*=.005) and 3-fold longer ICU LOS (incidence rate ratio=3.07, 95% CI 2.18-4.30; *P*<.001) after adjustment for age, comorbidities, frailty status, and pneumonia severity when compared to patients who were not deficient. There was a trend toward increased in-hospital mortality (adjusted odds ratio 4.23, 95% CI 0.58-30.48) and 30-day mortality (adjusted odds ratio 3.82, 95% CI 0.71-20.50) among patients who had vitamin C deficiency. Randomized trials evaluating vitamin C in the treatment of infections have yielded inconsistent results. While some studies suggest improvements in respiratory parameters, larger trials in patients with sepsis who are critically ill have not demonstrated a clear mortality benefit, potentially due to differences in patient populations, formulation, dosing strategy, and abrupt discontinuation of therapy [13-15]. Furthermore, evidence specific to hospitalized patients with CAP outside the ICU remains limited.

### Study Justification

Previous randomized controlled trials (RCTs) evaluating vitamin C in CAP have yielded inconsistent findings, with most research focused on patients with sepsis who are critically ill rather than hospitalized CAP populations [14,16,17]. A 2021 systematic review including 5 RCTs of oral and parenteral vitamin C reported modest reductions in time to improvement in oxygen saturation and respiratory rate, suggesting potential clinical benefit [13]. In contrast, the Lessening Organ Dysfunction With Vitamin C (LOVIT) trial, which evaluated high-dose intravenous ascorbic acid in patients with sepsis who were critically ill (one-third with respiratory infection), found no significant mortality benefit, although treatment was abruptly discontinued and ascorbic acid was used rather than sodium ascorbate [14]. Subsequent meta-analyses incorporating LOVIT trial data have reported low-certainty evidence, with point estimates favoring reductions in in-hospital (risk ratio [RR]=0.88, 95% CI 0.73-1.06) and 30-day (RR=0.83, 95% 0.71-0.98) mortality. Our recent CAP-specific systematic review demonstrated a nonsignificant trend toward reduced mortality (RR=0.51, 95% CI 0.24-1.09; *P* for overall effect =.05; *I*^2^*=*0%; *P* for heterogeneity=.65) [18,19]. The absence of benefit in LOVIT and similar trials may relate to rebound hypovitaminosis following abrupt cessation, increased metabolic consumption during sepsis, or formulation-related effects, as also observed in the Vitamin C Infusion for Treatment in Sepsis Induced Acute Lung Injury (CITRIS-ALI) study [20]. Overall, existing studies [14,17] are predominantly ICU based, frequently involve abrupt treatment discontinuation, and rarely assess patient-centered outcomes or symptom recovery. Therefore, expert consensus [16,20,21] highlights the need for rigorously designed trials evaluating sustained vitamin C replacement using sodium ascorbate in hospitalized patients with CAP, providing a strong justification for this study.

Thus, there is a clear evidence gap regarding the effectiveness of vitamin C supplementation as an adjunct therapy in hospitalized patients with CAP, particularly using oral sodium ascorbate and assessing patient-centered outcomes. The Vitamin C in Community-Acquired Pneumonia (VitCAP) trial is designed to address this gap by evaluating high-dose oral vitamin C administered over an extended period; avoiding abrupt cessation; and focusing on clinically meaningful end points, including time to clinical stabilization, symptom recovery, and health-related quality of life (HRQOL). This study aims to generate high-quality evidence to inform future clinical practice and guideline development.

### Study Aim and Hypotheses

The primary aim of the VitCAP trial is to determine whether high-dose oral vitamin C (sodium ascorbate) administered during hospitalization and continued for 30 days after discharge improves clinical recovery in adults hospitalized with CAP when compared with placebo alongside standard care. The primary hypothesis is that vitamin C supplementation will reduce the time to clinical stabilization compared with placebo.

Secondary hypotheses are that vitamin C supplementation will (1) improve early clinical response; (2) reduce hospital LOS; (3) decrease the need for intensive care, ventilatory support, or vasopressors; (4) reduce mortality and hospital readmission; (5) improve patient-reported symptom burden and HRQOL; and (6) reduce systemic inflammatory biomarkers, including C-reactive protein and procalcitonin.

## Methods

### Study Design

This study is a single-center, double-blind, placebo-controlled, parallel-group randomized clinical trial designed in accordance with the SPIRIT (Standard Protocol Items: Recommendations for Interventional Trials) 2013 statement. Participants will be randomly allocated in a 1:1 ratio to receive either high-dose oral vitamin C (as sodium ascorbate) or a matching placebo in addition to standard care for CAP (Figure 1).

**Figure 1 figure1:**
[figure not shown]
Flow diagram for the Vitamin C in Community-Acquired Pneumonia trial. CURB-65: confusion, urea, respiratory rate, blood pressure, and age ≥65 years; eGFR: estimated glomerular filtration rate; G6PD: glucose-6-phosphate dehydrogenase.

### Study Setting

The trial will be conducted at a tertiary hospital in Australia providing acute general medical and respiratory services. Recruitment will be conducted among patients admitted under general medicine, respiratory, or intensive care teams with a primary diagnosis of CAP.

### Eligibility Criteria

The eligibility criteria have been provided in Textbox 1.

Eligibility criteria.
**Inclusion criteria**
Age of 18 years or olderHospital admission with community-acquired pneumonia (clinical symptoms of cough, sputum production, dyspnea, and fever, along with imaging evidence of an infiltrate)Randomization within 48 hours of hospital admissionAbility to provide informed consent or availability of a legally authorized representative
**Exclusion criteria**
Hospital-acquired or ventilator-associated pneumoniaSevere renal impairment (estimated glomerular filtration rate <30 mL per minute per 1.73 m^2^)Known glucose-6-phosphate dehydrogenase deficiencyHistory of nephrolithiasis or hemochromatosisPregnancy or breastfeedingCurrent use of vitamin C supplements

### Interventions

Participants allocated to the intervention arm will receive *oral sodium ascorbate* (*1 g 3 times daily for 7 days,* followed by *500 mg twice daily for 30 days*). The control group will receive a matching placebo administered using the same dosing schedule. The placebo consists of capsules containing Starch 1500 (partially pregelatinized maize starch; Colorcon, Inc) as an inert excipient. The placebo material will be encapsulated in white opaque size 0 Coni-Snap hard gelatin capsules (Lonza). Active and placebo capsules will be matched in size, color, and appearance to maintain blinding. Adherence will be assessed through medication administration records during hospitalization and participant self-report after discharge.

All participants will receive standard CAP management in accordance with local clinical guidelines. Standard management for hospitalized patients with CAP at the study center follows national and local clinical guidelines. Initial management typically includes early administration of empirical antibiotics according to pneumonia severity and risk factors and supportive care, including oxygen therapy when required, intravenous fluids, venous thromboembolism prophylaxis, and monitoring of vital signs and laboratory markers of infection. Patients with severe disease may receive care in the intensive care settings and may require respiratory or hemodynamic support.

The vitamin C dosing regimen for this trial was selected to rapidly correct hypovitaminosis C during the acute illness phase (1 g 3 times daily for 7 days) and maintain adequate plasma concentrations during recovery (500 mg twice daily for 30 days). Oral sodium ascorbate was chosen for its high bioavailability, tolerability, and practicality for prolonged administration in both hospital and postdischarge settings. This approach avoids abrupt cessation and potential rebound deficiency observed in previous trials such as LOVIT [14] and CITRIS-ALI [20].

### Outcomes

The primary outcome is *time to clinical stabilization*, defined as the time from randomization to meeting all the criteria.

The primary and secondary outcomes have been provided in Textbox 2.

Primary and secondary outcomes.
**Primary outcome**
Temperature of 37.8 °C or lessHeart rate of 100 beats per minute or lessRespiratory rate of 24 breaths per minute or lessSystolic blood pressure of 90 mm Hg or higherOxygen saturation of 90% or higher or arterial partial pressure of oxygen of 60 mm Hg or higher on room air
**Secondary outcomes**
Early clinical response [22], defined as improvement in at least 2 of 4 specific symptoms (chest pain, cough, sputum production, and dyspnea) without any symptom worsening 3 to 5 days after randomizationImprovement in community-acquired pneumonia–related symptoms at 30 days from the day of randomization, measured using the 18-item community-acquired pneumonia symptom questionnaire [23] (range 0-90)Intensive care unit admissionRequirement for noninvasive or invasive mechanical ventilationVasopressor useLength of hospital stayAll-cause mortality at 30 days and 6 months30-day hospital readmissionHealth-related quality of life at 1 and 6 months using the EQ-5D-5L [24]Inflammatory biomarkers (C-reactive protein and procalcitonin) measured at baseline and day 7 or discharge

### Sample Size Calculation

The sample size was based on a previous RCT [16], which reported that the mean time to clinical stabilization (used as a proxy for hospital discharge) in patients with CAP was 3.6 (SD 1.9) days in patients who were in the vitamin C group compared to 4.7 (SD 2.0) days in the placebo group. Using this effect size (1.1 days), a pooled SD of 1.95, a power of 80%, and a 2-sided α of .05, the required sample size is 102 participants (51 per group). To account for an anticipated 20% attrition rate due to loss to follow-up or mortality, we plan to recruit 124 participants (62 per group).

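### The recruitment target of 124 does not preserve the required 102 under the stated 20% attrition; it leaves about 99, and t-test power of 79.4%

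*Protocol article*

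**What the plan says.** The calculation is in the protocol article, Methods, Sample Size Calculation. It takes the means and standard deviations of an earlier randomized trial (3.6, SD 1.9, against 4.7, SD 2.0) and fixes its inputs as follows: "Using this effect size (1.1 days), a pooled SD of 1.95", with "a power of 80%, and a 2-sided α of .05". From these it concludes that "the required sample size is 102 participants (51 per group". The next sentence adds the allowance for losses: "To account for an anticipated 20% attrition rate due to loss to follow-up or mortality, we plan to recruit 124 participants (62 per group".

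The target of 124 appears in two other places. The Results paragraph of the abstract says "A total of 124 participants will be enrolled to provide 80% power" and adds that this allows for attrition, without giving a rate. The main Results section repeats 124 with 80% power and does not mention attrition. The 20% figure stands only in the Sample Size Calculation section.

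**The concern.** An attrition rate is a share of those recruited. To end with 51 per group after losing 20%, recruitment must be 51 divided by 0.8. The stated 62 per group is what results when 20% of the evaluable number is added to it, and this always falls short of the requirement, apart from any help from rounding. The section therefore prints a required number, an anticipated loss and a recruitment target that cannot all hold. This figure is the basis of the trial's power statement, and the slip runs in the favourable direction.

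**Working it through.** **Inputs.** From Sample Size Calculation: difference 1.1 days, SD 1.95, two-sided α 0.05, power 80%, required 51 per group (102), attrition 20%, recruitment 62 per group (124). From Study Design: 1:1 allocation.

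**1. Reproduce the required number.** The standardized difference is d = 1.1/1.95 = 0.564. Solving the two-sample t-test for 80% power gives 50.31 per group, rounded up to 51, or 102 in total. This matches the plan exactly; power at 51 per group is 80.5%. The normal approximation, 2 × (1.95 × (1.960 + 0.842)/1.1)², gives 49.33, so 50 per group (100). The stated 51 is therefore the t-test result, and the base calculation is sound.

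**2. Reproduce the recruitment target.** Two ways of applying 20% to 51 per group:

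| Form | Per group | Rounded up | Total |
|---|---|---|---|
| n × (1 + 0.20) | 51 × 1.2 = 61.2 | 62 | 124 |
| n / (1 − 0.20) | 51 / 0.8 = 63.75 | 64 | 128 |

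Only the first gives the plan's 124. Starting from the normal approximation does not explain it either: 50/0.8 = 62.5, so 63 per group and 126 in total, and that route abandons the stated 51.

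**3. Apply the plan's attrition to the plan's target.** 124 × 0.8 = 99.2, or 62 × 0.8 = 49.6 per group. This is 102 − 99.2 = 2.8 participants below the requirement.

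**4. Attrition that 124 can absorb.** 1 − 102/124 = 0.177, so 17.7%.

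**5. Power after 20% attrition** (d = 0.564, two-sided α 0.05):

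| Recruited | Evaluable per group | t-test power |
|---|---|---|
| 124 | 49.6 | 79.4% |
| 126 | 50.4 | 80.1% |

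With 128 recruited, 51.2 per group remain, which keeps the stated 51 (80.5%). At 49.6 per group the normal approximation gives 80.2%. The difference detectable with 80% t-test power at 49.6 per group is 1.108 days, against the planned 1.1. The gap is 0.008 days, or about 12 minutes (0.008 × 24 × 60 = 11.5).

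**The case against.** The strongest reply is that 99 is not the number the primary analysis will use. Statistical Methods includes all randomized patients, the primary model is a Cox regression that accounts for censoring, and multiple imputation is planned for missing data. The endpoint is read from daily inpatient observations, with assumed means of 3.6 and 4.7 days, so a patient lost at the 30-day or 6-month telephone call has normally already contributed. The Introduction cites in-hospital mortality of 7.8%. If in-hospital death were the only loss, which is an assumption, 124 × 0.922 = 114 would remain, more than 102. This stands, and it limits what may be concluded about real loss of power. It does not reconcile the section, which chose 20% as its own allowance and applied it to a comparison of means.

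A second reply is that the effect is negligible beside the uncertainty of an effect size and SD taken from one earlier trial. That also stands as a judgement of size. It does not make the printed figures agree.

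A third is that an article condenses a fuller protocol. Here nothing is missing except the inflation formula: the inputs and the result are all printed, and they disagree whichever formula was used.

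Three stronger readings are tempting, and the document supports none of them:

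- *The abstract and Results section also claim 80% power at 20% attrition.* They do not. The abstract gives no rate, and the Results section does not mention attrition.
- *128 participants are needed for 80% power.* They are needed to keep the rounded-up 102. On the power criterion alone, 126 is enough.
- *The trial is materially underpowered because of this step.* The shortfall is under 1 percentage point by the t-test and disappears under the normal approximation.

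**Conclusion.** The point holds as a small arithmetic inconsistency within one section. The required 102, the 20% attrition and the target of 124 cannot all stand. On the plan's own premise 124 leaves about 99 evaluable (49.6 per group) and t-test power of 79.4%, and it preserves 102 only up to 17.7% attrition. The inflation that matches 102 and 20% is 128, which is 4 more than stated.

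The conclusion rests on reading attrition as a share of those recruited and as removing patients from a comparison of means, as the section's allowance implies. That 51 × 1.2 was the route to 62 is inferred from an exact match, but the inconsistency does not depend on it. The design and the planned analyses are not put in doubt.

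**What to change.** Amend the attrition sentence in Sample Size Calculation in one of two ways, neither of which needs more patients:

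- State that 124 participants with 20% attrition leave about 99 evaluable and about 79% power by the t-test calculation. This fits best if 20% remains the rate the sponsor expects.
- State that 124 preserves the required 102 only up to 17.7% attrition. This should be worded as what the target tolerates, not as a new expected rate fitted to the total.

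If the sponsor prefers to keep both 20% attrition and the stated 102, the matching total is 128 (64 per group), 4 more participants. If it is enough that t-test power reaches 80% after 20% attrition, 126 (63 per group) does so with 2 more.

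Whichever is chosen, check that the 80% power statements in the abstract and the Results section remain consistent with it. Restating costs one sentence and a slightly less favourable figure, and it is easily done now because the article describes recruitment as still to begin.

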### Randomization and Allocation Concealment

Randomization will be performed using a computer-generated sequence with variable block sizes and stratification by pneumonia severity. Allocation concealment will be ensured via a centralized pharmacy service responsible for dispensing sequentially numbered, identical study medications.

### Blinding

Participants, treating clinicians, investigators, outcome assessors, and statisticians will remain blinded to treatment allocation. Study medications will be indistinguishable in appearance, taste, and packaging. Emergency unblinding will be permissible only when knowledge of allocation is essential for clinical management.

### Data Collection and Follow-Up

Clinical data will be collected daily during hospitalization. Follow-up assessments will be conducted at 30 days and 6 months after randomization via telephone interview. Data will be recorded using secure electronic case report forms. The schedule of enrollment, interventions, and outcome assessments is summarized in Table 1.

**Table 1 table1:** Schedule of enrollment, interventions, and assessments for the Vitamin C in Community-Acquired Pneumonia trial.

	Screening and baseline	Day 0—randomization	Days 1-7—hospital phase	Day 30—follow-up	Month 6—follow-up
Eligibility assessment	✓				
Informed consent	✓				
Randomization		✓			
Vitamin C or placebo administration		✓	✓	✓	
Clinical observations (vital signs)	✓	✓	✓^a^		
CAP^b^ symptom assessment	✓		✓	✓	
Early clinical response assessment			✓^c^		
Inflammatory biomarkers (CRP^d^ and PCT^e^)	✓		✓^f^		
Hospital outcomes (ICU^g^ admission, ventilation, and vasopressor use)			✓		
Length of stay			✓		
Adverse event monitoring		✓	✓	✓	✓
Hospital readmission				✓	
Health-related quality of life (EQ-5D-5L)				✓	✓
Mortality assessment			✓	✓	✓

^a^Daily during hospitalization (days 1-7).

^b^CAP: community-acquired pneumonia.

^c^Assessed on days 3-5.

^d^CRP: C-reactive protein.

^e^PCT: procalcitonin.

^f^Measured on day 7 or at discharge (whichever occurs first).

^g^ICU: intensive care unit.

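### Early clinical response is due on days 3 to 5, but the schedule has no symptom contact in that window for participants already discharged, and that loss depends on recovery speed

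*Protocol article*

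**What the plan says.** Textbox 2 (Outcomes) defines early clinical response as improvement in at least two of four symptoms, with none worse, 3 to 5 days after randomization. Improving it is also the first secondary hypothesis.

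Table 1 (Data Collection and Follow-Up) ticks this assessment once, in the hospital-phase column for days 1 to 7. Footnote c reads "Assessed on days 3-5". The text above the table describes two modes of collection: "Clinical data will be collected daily during hospitalization. Follow-up assessments will be conducted at 30 days and 6 months after randomization via telephone interview".

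The inflammatory biomarkers have a rule for early discharge. Footnote f reads "Measured on day 7 or at discharge (whichever occurs first". Early clinical response has none.

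Sample Size Calculation takes its planning figures from an earlier trial's "mean time to clinical stabilization (used as a proxy for hospital discharge", giving "3.6 (SD 1.9) days in patients who were in the vitamin C group compared to 4.7 (SD 2.0) days in the placebo group". Secondary Outcome Analysis names multiple imputation for missing data in general terms.

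**The concern.** The outcome window is counted from randomization, but the only early data collection described depends on still being in hospital. The next scheduled contact is the day-30 call. A participant who goes home on day 1 or 2 therefore has no scheduled occasion on which the four symptoms are compared with baseline inside the window.

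The participants lost are the fastest to recover. The protocol hypothesizes a shorter stay on vitamin C, so if the treatment works, more of the lost participants will be in that arm. A comparison restricted to those assessed would then leave out early recoverers unequally and would tend to understate a benefit. If vitamin C has no effect, losses should be similar in the two arms. The main risk is thus a diluted estimate when a benefit exists.

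An analysis plan can say how to handle such gaps, but it cannot supply symptom data that nobody collected.

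**Working it through.** **The plan's own figure.** No sample size, power or discharge distribution is stated for early clinical response. The nearest figure is the sample size for the primary outcome: "Using this effect size (1.1 days), a pooled SD of 1.95, a power of 80%, and a 2-sided α of .05". The two-sample t-test solution is 50.3, so 51 per group and 102 in total, with power 0.805. That reproduces the plan. The recruitment target of 62 per group is used below to turn shares into counts.

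**Inputs.** Means and SDs are 3.6 (1.9) days on vitamin C and 4.7 (2.0) days on placebo, from Sample Size Calculation. The window opens at day 3, from Textbox 2.

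**Assumption.** These figures are treated as time T from randomization to discharge. The protocol links stabilization to discharge only as a proxy, so the timing is varied below.

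**Share leaving before day 3, P(T < 3).**
- Normal: Φ((3 − 3.6)/1.9) = Φ(−0.316) = 0.376; Φ((3 − 4.7)/2.0) = Φ(−0.85) = 0.198.
- Gamma (shape = mean²/SD², scale = SD²/mean): 0.438 and 0.202.
- Lognormal (σ² = ln(1 + SD²/mean²), median = mean/√(1 + SD²/mean²)): 0.452 and 0.185.

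Out of 62 per arm this is 23–28 on vitamin C (62 × 0.376 = 23.3; 62 × 0.452 = 28.0) and 11–13 on placebo (62 × 0.185 = 11.5; 62 × 0.202 = 12.5).

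**Sensitivity to timing** (ranges span the three shapes):

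| Reading of the planning figures | Computed as | Vitamin C | Placebo |
|---|---|---|---|
| Days from randomization to discharge | P(T < 3) | 38–45% | 19–20% |
| Discharge 1 day later than the figures | P(T < 2) | 17–20% | 3–9% |
| Discharge 2 days later | P(T < 1) | 1–9% | 0–3% |
| Counted from admission, randomization 1 day later | P(T < 4) | 58–68% | 36–42% |

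Eligibility allows randomization up to 48 hours after admission, so the last row is possible. It is somewhat high, because it does not condition on still being in hospital at randomization. With the normal shape, conditioning gives (0.583 − 0.086)/(1 − 0.086) = 54% and (0.363 − 0.032)/(1 − 0.032) = 34%.

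In every row more vitamin C participants go unassessed. That follows from assuming the planned benefit.

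**Purely illustrative effect on the estimate.** The response rates here are assumed and have no source in the documents. Suppose true response is 70% against 55%, a 15-point difference, and the shares lost are 0.376 and 0.198.
- If 90% of those lost are responders, response among the assessed is (0.70 − 0.376 × 0.9)/0.624 = 57.9% and (0.55 − 0.198 × 0.9)/0.802 = 46.4%, a difference of about 12 points.
- If all of those lost are responders, it is (0.70 − 0.376)/0.624 = 51.9% and (0.55 − 0.198)/0.802 = 43.9%, a difference of 8 points.

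**The case against.** **The article may have condensed a fuller schedule.** Footnote c gives the days without an inpatient condition, whereas footnotes a and f refer to hospitalization or discharge. The hospital-phase column also carries study-drug administration, and the 7-day first phase of dosing is not made conditional on stay. A telephone assessment may therefore be intended. This stands as a caution: the documents do not say that early clinical response is limited to inpatients. But the text lists the follow-up contacts and none falls on days 3–5. Telehealth follow-ups appear under Consumer Engagement only among strategies still to be developed.

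**A reader might infer that no data at all are collected between discharge and day 30.** That is not so. Adverse events are recorded from randomization to the end of follow-up, and adherence is self-reported after discharge. Table 1 also has symptom assessments at baseline, in days 1–7 and at day 30. None of these gives the four-symptom comparison on days 3–5 for someone already home.

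**A reader might take 38–45% against 19–20% as the expected loss.** The documents do not support that. The figures describe a proxy, and a 2-day lag to discharge nearly removes the problem. The cut-off matters too: if randomization is at midday, calendar day 3 opens at about 2.5 days, and the normal model gives Φ(−0.579) = 28% and Φ(−1.1) = 14%.

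**A reader might infer that the benefit would be wiped out.** Assumed rates can be chosen to show this. With 90% response in those discharged early and 50% in the rest of both arms, the true difference is (0.376 × 0.9 + 0.624 × 0.5) − (0.198 × 0.9 + 0.802 × 0.5) = 7 points, and the difference among the assessed is zero. But that zero is built into the choice of 50% in both arms. Counting the unassessed as non-responders would look worse still, but the protocol does not propose it.

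**A reader might infer that multiple imputation must fill the gaps from sicker inpatients.** The imputation model is not shown and belongs in the analysis plan. It could use in-hospital symptoms, discharge timing and day-30 symptoms. What remains true is that no one discharged before day 3 would have an observed value in the window, so any such model would rest on assumptions the data cannot check.

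**Conclusion.** The point holds as a gap in the assessment schedule. Followed as written, participants discharged before day 3 have no scheduled assessment of early clinical response in its window. Those leaving on days 3–5 can still be assessed before they go. The missingness is tied to recovery speed, so it is informative, and it would be unequal between arms if vitamin C shortens the stay.

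The direction is well supported, but the size is not. Across the timings tried, the share lost runs from 1–9% against 0–3% up to 58–68% against 36–42% (vitamin C against placebo). All of these depend on reading the earlier trial's figures as discharge times. The bias figures are illustrations only.

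The outcome is secondary, and neither the primary analysis nor the sample size is affected. The change should be made because the lost data cannot be recovered later and the remedy is small.

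**What to change.** Amend Table 1 (the early clinical response row and footnote c) and the Data Collection and Follow-Up text so that the four symptoms are assessed on days 3–5 in every randomized participant. This would be done at the bedside if the participant is still admitted, and otherwise by a brief telephone call from the existing research staff. Record the last in-hospital symptom assessment as an auxiliary value for imputation, or as the stated fallback if the call fails. If a day 3–5 call is already intended, saying so in both places is enough.

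The cost is a protocol amendment, ideally before the first participant is enrolled, and a limited number of four-question calls by a team that already conducts telephone interviews. The downside is a mix of bedside and telephone mode. Because earlier discharge could make telephone mode more frequent in one arm, the mode should be recorded for each assessment.
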